Immediately upon completion of each of the 5 CFT or CFT + AAR team meetings, the CWS caseworkers together with ~ 7 additional CFT members will provide data a via web-based online survey to assess mechanisms and outcomes. This results in 8 caseworkers leading 5 CFTs each for a total of 40 unique CFTs. Each of the 40 CFTs has ~8 participants, for a minimum total of 320 data points. See Fig. 2 for sampling.

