#### McAllister affect-based trust

This 5-item scale [58] assesses perceptions of affect-based trust amongst CFT members. Items center on individual’s perceptions that team members can share ideas freely, that team members listen to one another, that team members care for one another, and that team members are invested in working well with one another. Each participant will complete this measure immediately following their completion of the intervention. Participants respond on a scale ranging from 1 = strongly disagree to 7 = strongly agree, and scale scores are computed by calculating the average item response.

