#### Parent Participation Engagement Measure (PPEM)

This 5-item measure originally developed for culturally diverse families served in children’s outpatient mental health, was adapted for CWS home visitation services, and assesses active parent participation, engagement, and voice in treatment services [59]. Each participant will complete the PPEM immediately following their completion of the intervention. Participants respond on a 5-point Likert-type scale ranging from 1 = not at all to 5 = very much. Scale scores are computed by calculating the average item response.

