#### Working Alliance Inventory Short Form (WAI-SR)

The WAI-SR [60] is a 12-item version of the Horvath and Greenberg’s (1989) Working Alliance Inventory. Each item is responded to using a 7-point Likert-type scale. It yields three summed subscale scores, as well as one summed overall scale score. Each of the subscales will measure proposed mechanisms, while the overall scale will measure proposed outcomes. The 4-item Goal subscale will be used to determine team member agreement on goals for CWS child/family case treatment plan (goal specification). The 4-item Task subscale will be used to determine team member agreement on how to achieve goals for CWS child/family case treatment plan (strategy formulation). The 4-item Bond subscale will be used to determine the personal bond between CFT team members (trust). The overall scale score assesses the collaborative relationship between relevant parties and consensus and willingness by all to engage in and do the work that leads to improvement (CFT Fidelity). Each participant will complete the WAI-SR immediately following their completion of the intervention.

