### Data management

All collected data will use codes rather than subject names. Only the primary research team members will have access to participant identifiers. The research team will use a university-approved data entry, training, and management system that complies with the data security requirements of the Health Insurance Portability and Accountability Act of 1996 (HIPAA) [61] and the Health Information Technology for Economic and Clinical Health (HITECH) Act [62]. Aim 1 qualitative interview data will be de-identified and transcribed by study personnel or HIPAA compliant transcription services. Survey data for Aim 3 will be collected electronically at the end of the CFT meeting using secure online survey program software, with individual distribution links shared at the end of the CFT meeting. Web-survey data and qualitative transcripts kept by the research project will be coded with a unique identifying number for which the key will be separately stored and limited to primary research staff members who will only share these data to the extent necessary for required reporting purposes. Audio recording data from interviews and focus groups will be uploaded by study staff securely to the HIPAA compliant server.

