### Analytic plan

Multilevel modeling with random intercepts and slopes will be used to examine differences in the targeted outcomes between CFT and CFT + AAR conditions, while accounting for the nested data structure. Specifically, this project will test the main effect of the AAR on implementation outcomes and child/family outcomes. Analyses will include the between-CFT meeting factor of condition (CFT vs. CFT + AAR) and within-CFT meeting factor of individual CFT member participant. The cross-level condition by participant interaction effect on the specified outcomes will be of primary interest.

A cross-level prediction model will test the extent to which the condition effect on the CFT outcomes is mediated by its proximal effect on team processes and emergent states. To assess the extent to which team processes are targeted by the AAR intervention, the Goal and Task subscales of the Working Alliance Inventory-Short Revised (WAI-SR) will be used to assess goal specification and strategy formulation, respectively [60, 63]. The Collaboration subscale of the Collaboration & Satisfaction About Care Decisions (CSACD) [57] measure will be used to assess the extent to which the AAR engages the team processes of communication and coordination. Several measures will be used to assess the extent to which emergent states are targeted by the AAR. Specifically, the Bond subscale of the WAI-SR and the McAllister Affect-Based Trust [58] measure will be used to assess trust. Edmondson’s Psychological Safety Climate [41] measure will assess the extent to which the AAR impacts the emergent state of psychological safety. To assess the extent to which the AAR engages the emergent state of shared mental models, a card-sorting task will assess CFT team shared mental models by examining perceptions of member roles, responsibilities, and goals across CFT team members. The concepts contained in the card sort will be representative of specific CFT roles, task responsibilities, and goals. To determine the feasibility, acceptability, and appropriateness of the AAR for CWS CFTs, those in the CFT + AAR condition will complete the Feasibility, Acceptability, and Appropriateness of Intervention Measures, respectively [51].

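### For the fidelity and satisfaction outcomes, rated mediators and outcomes come from the same person in the same survey, so an apparent mechanism may be a rating artefact

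*Protocol article*

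**What the plan says.** The Analytic plan section specifies a cross-level model of whether "the condition effect on the CFT outcomes is mediated by its proximal effect on team processes and emergent states". Specific aim 3 has the caseworker and about seven other members report after each meeting "via web-based online survey to assess mechanisms and outcomes". The Data management section confirms the timing: "Survey data for Aim 3 will be collected electronically at the end of the CFT meeting using secure online survey program software".

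The Measures section and Table 1 assign the roles:

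- **Rated mediators:** WAI-SR Goal, Task and Bond, CSACD collaboration, affect-based trust and psychological safety.
- **Rated outcomes:** WAI-SR overall and PPEM (fidelity), and CSACD satisfaction.

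Timing and respondent are the same on both sides. For trust, a mediator: "Each participant will complete this measure immediately following their completion of the intervention". For PPEM, an outcome: "Each participant will complete the PPEM immediately following their completion of the intervention". The WAI-SR supplies both roles: "Each of the subscales will measure proposed mechanisms, while the overall scale will measure proposed outcomes".

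Two measures differ in kind. The card sort is a sorting task compared across members, and service linkage comes from County administrative records. Specific aim 3 states that allocation is neither concealed nor blinded. The Power analysis section calls the mediation tests preliminary, and the only reason it gives is limited power.

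**The concern.** The mechanistic model has a time order: emergent states and processes come first, then fidelity, then satisfaction, then linkage. Before linkage, the planned measurement gives that order no support. Randomising condition identifies its effect on each mediator, but the mediator-to-outcome path remains an observational correlation. Here it is a correlation between two ratings by one person at one moment. Someone who leaves the meeting pleased may rate safety, trust, engagement and satisfaction all high, or satisfaction may colour the reported trust. Either would appear as a mediator-to-outcome path.

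Exploring team mechanisms is a stated purpose of Aim 3. At stake is whether the trial can say that the AAR improved fidelity or satisfaction through, for example, psychological safety. More data would not remove this bias; it would only estimate it more precisely.

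**Working it through.** **Plan's own figure.** The Power analysis section gives an effective sample of 36: 320 / [1 + (40 − 1) × 0.20] = 320 / 8.8 = 36.4, so it reproduces with a cluster size of 40. Whether 40 is the right cluster size is a separate matter.

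**Inputs from the article.** 8 caseworkers × 5 meetings = 40 CFTs (20 per arm), about 8 respondents each, within-meeting correlation 0.20.

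**Assumptions, not in the article.** Shared rater variance λ = 0.10, 0.20 or 0.30; AAR shift of the rated mediator d = 0.5 or 0.2 SD; no true effect of condition or mediator on the outcome.

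**Model, total variance 1.** Mediator M = d·arm + u + h + e. Outcome Y = v + h + e′. The meeting effects u and v have variance 0.20 each, the rater's shared tendency h has variance λ, and each residual has variance 0.80 − λ. The true mediator-to-outcome path is zero.

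**Expected spurious indirect effect at d = 0.5, with u and v independent.**

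- Pooled individual path: b = λ / 1, so the indirect effect is 0.5λ = 0.05 / 0.10 / 0.15 SD.
- Meeting-mean path: covariance λ/8, variance 0.20 + 0.80/8 = 0.30, so b = λ/2.4 = 0.042 / 0.083 / 0.125 and the indirect effect is 0.02 / 0.04 / 0.06 SD. Averaging over eight raters dilutes the shared tendency.
- Mean of the other seven members: no shared rater term, so the indirect effect is 0.

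**Ceiling on false claims.** Joint significance also needs the condition-to-mediator path. Its standard error is √(0.30 × (1/20 + 1/20)) = 0.173, so d = 0.5 gives 0.5/0.173 = 2.89 and d = 0.2 gives 1.15. Against a critical value of 2.02, power is roughly 0.81 and 0.19. False-claim rates cannot rise much above these values.

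**Simulated false mediation (joint significance, nominal 5%).**

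| Mediator-outcome path | Shift | λ = 10% | 20% | 30% |
|---|---|---|---|---|
| Pooled individual | 0.5 SD | 29% | 71% | 79% |
| Pooled individual | 0.2 SD | 8% | 17% | 21% |
| Meeting mean | 0.5 SD | 4% | 6% | 10% |
| Other members' mean | 0.5 SD | 6–7% | 6–7% | 6–7% |

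With no shift of the mediator, all rates are about 5% or lower. Testing the condition-to-mediator path on the eight caseworker means (the randomised unit) lowers the first row to 25/60/68%. A cruder check with 36 independent observations and a 0.8 SD shift gives 5.5/14/26% for the same λ.

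**Limit of the other-member mediator.** Suppose u and v correlate 0.5, because some meetings simply go well. The covariance is 0.5 × 0.20 = 0.10 and the variance of the seven-member mean is 0.20 + 0.80/7 = 0.314. Then b = 0.32, the spurious indirect effect is 0.16 SD, and false claims run at about 45–50%. The meeting-mean path is no safer: at λ = 0.10, b = (0.10 + 0.0125)/0.30 = 0.375.

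**WAI-SR special case.** The overall score is the sum of the same items as its subscales: "It yields three summed subscale scores, as well as one summed overall scale score". A subscale correlates with the total at (1 + 2r)/√(3 + 6r), where r is the correlation between subscales. That is 0.58 at r = 0 and 0.82 at r = 0.5, by scoring alone.

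**The case against.** The strongest reply concerns size. The 29/71/79% figures need a pooled individual-level path and a 0.5 SD shift. The article plans multilevel, cross-level models with condition varying between meetings, and it describes psychological safety as a group-level construct. A meeting-mean path on the same data stays near the nominal rate at 10–20% shared variance. The article does not fix the level of the path, and an article commonly leaves that to the full plan. This stands: the high rates cannot be attributed to the planned test. They show what one admissible reading of it would do.

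A reader might infer that the trial cannot address its mechanism objective at all, or that every mediator is a self-rating. The documents support neither. The card sort is a listed mechanism measure and not a satisfaction-type rating, though it shares respondent and timing. Linkage is a listed outcome from another source, and the condition effect on each mechanism keeps its randomised basis.

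It is also fair that Aim 3 is a pilot that explores mechanisms, with tests called preliminary. That lowers the stakes, but the stated caveat is power, which does not cover a bias that persists at any sample size. Finally, other members' ratings answer a somewhat different question (their felt safety, not the caregiver's), and restricting claims to linkage leaves about 40 CFT-level outcomes. Both points stand and limit what the fix can deliver.

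**Conclusion.** The concern holds for one set of pairs: rating-scale mediators with PPEM, CSACD satisfaction or WAI-SR overall. For these, an apparent indirect effect can arise from shared rating tendency or reverse order, provided the AAR moves the rated mediator, which is the trial's own hypothesis. The false-claim rate ranges from about nominal (meeting-mean path, modest shared variance, independent meeting effects) to about 79% (pooled path, 30% shared variance, 0.5 SD shift). Shared variance, shift and the correlation of meeting effects are all assumed. The range therefore shows sensitivity to the unstated level of the path and does not forecast this trial's error rate. The WAI-SR subscale-to-total pairs are affected by scoring, whatever the shared rating variance. The change is worth making because it alters what the trial may conclude and needs no new data.

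**What to change.** Amend the analysis wording, using data already planned:

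1. Report same-rater, same-survey mediator-outcome associations as descriptive, and claim no mechanism from them.
2. Separate the within-meeting from the between-meeting path, and do not use the pooled individual-level path for the indirect effect.
3. Add a sensitivity analysis with the mean rating of the other members of the same CFT as mediator. State that it removes the individual's rating tendency but not team-level confounding.
4. Report mediation of administrative linkage as the separate-source, later-in-time analysis, labelled exploratory and with low power at about 40 CFTs.

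The cost is lower precision on the mediator-to-outcome path, a changed question in item 3, and more modest mechanism claims. No extra measurement or contact with participants is needed.

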### Power analysis

Based upon the sampling strategy, power analysis was conducted to inform the detectable magnitude of effect. Power for the primary CFT services intervention outcomes, and team processes/emergent states outcomes, was estimated using a multi-step approach recommended by Hox [64]. First*,* a total number of observations was computed while ignoring nesting. With 8 team members from 8 child-family teams (4 per region) participating in data collection following each of 5 child-family team meetings, there is a total of 320 observation results. For these observations, the nested data structure introduces dependency that decreases the level of statistical power. To adjust for this, a second step was to penalize the total sample for nesting. This was accomplished using a reorganization of the design effect formula (i.e., *n*_*eff*_ = *n*/[1 + [*n*_*clus*_ − 1]*ρ*]), which provides the effective sample size of independent observations. Using conservative nesting effects for CFT members within CFT meetings, *ρ* = 0.20, the 320 observations provide statistical power equivalent to 36 independent observations. Third, the effective sample size was used to perform conventional, single-level power analysis using GPower. Assuming power of 0.80 and *α* = 0.05, results indicated that a small-to-medium main effect of *f*^2^ = 0.10 for condition on CFT clinical intervention outcomes may be detected. As noted, for the preliminary mediation tests, statistical power is necessarily limited. Simulations performed by Fritz and MacKinnon [65] have demonstrated that required sample sizes for mediated effects range from 35 to 74. This depends on the magnitude of the effects for the respective paths, with the smaller sample sufficient if both paths have large effects and the larger sample sufficient if both paths have medium effects. As such, the effective sample size of 36 is potentially sufficient if the magnitude of each effect for the respective paths is great.

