**Methods:**

Using a parallel group trial design, with non-equivalent comparison groups, and qualitative and quantitative methodology, this study will tailor and assess the impact of the AAR on enhancing CFT outcomes. The authors will conduct a qualitative needs assessment targeting the ongoing implementation of the CFT services intervention in a large, publicly funded, CWS system. A qualitative inquiry consisting of interviews and focus groups with key stakeholders will result in the preparation of an action plan to address identified gaps between the current and desired CFT services intervention outcomes. The AAR implementation strategy will be adapted and tailored to address the CFT services’ intervention needs. To test the effectiveness of the AAR on improving outcomes associated with the CFT services intervention, we will utilize blocked randomization of four CWS caseworkers from two CWS system regions to either the intervention condition (CFT + AAR) or standard implementation (CFT as usual). The authors will collect data from the CWS caseworkers and additional CFT members via web-based surveys. Mechanisms of the AAR team effectiveness intervention for CFT implementation will be assessed.

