**Outcomes**			
Feasibility of Intervention Measure (FIM)	AAR Team Implementation Strategy Feasibility		✓
Acceptability of Intervention Measure (AIM)	AAR Team Implementation Strategy Acceptability		✓
Intervention Appropriateness Measure (IAM)	AAR Team Implementation Strategy Appropriateness		✓
Working Alliance Inventory-Short Revised (WAI-SR) Overall Score	CFT Clinical Intervention Fidelity Overall collaborative relationship	✓	✓
Parent Participation Engagement Measure (PPEM)	CFT Clinical Intervention Fidelity Collaboration and engagement	✓	✓
Collaboration & Satisfaction About Care Decisions (CSACD)—Satisfaction	CFT Clinical Intervention Outcome Satisfaction with decisions	✓	✓
SD County Behavioral Health Administrative Data	CFT Clinical Intervention Outcome Behavioral Health Service Linkage	✓	✓

Within team environments, shared mental models refer to the degree to which individual team members perceive key concepts (i.e., team, task) in a similar manner. For the CFT services intervention, shared mental models regarding perceptions of member roles, responsibilities, and goals can mediate more effective and efficient treatment planning. Team affect (i.e., trust and psychological safety) may also serve as mechanisms mediating success of the CFT services intervention. Psychological safety, a group-level phenomenon that correlates with team learning behaviors and performance, facilitates team members’ feelings of security [39] and focus on collective goals and problem prevention, rather than on self-protection [40–44]. Similarly, team trust is associated with decreased inefficiencies, greater negotiating effectiveness, and greater team effort, thus mediating overall team effectiveness [45–47]. Given the sensitivity and high stakes associated with CFT meetings (i.e., child placement, reunification), CFT members—particularly children/family—may feel uncomfortable fully participating for fear of negative repercussions. When CFT members experience enhanced shared mental models, psychological safety, and trust, they may be more open and willing to voice their opinions to collaborate on the treatment planning process for the CWS case.

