**Fig. 2 Fig2:**
[figure not shown]
Participant sampling strategy. *Note.* Participant sampling by team, CWS caseworker, and condition. In total, 320 assessments will be collected from project participants from two County regions—8 team members from 8 child-family teams (4 per region) will participate in data collection following each of 5 CFT meetings. Half will be assigned to the control, CFT as usual, and the other half will be assigned to the intervention, CFT + AAR. Sampling is mirrored for Region 2

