#### Card-sorting task

Card sorting elicits individual mental models to understand how participants structure their knowledge. In open card sorts, participants are provided with a set of key concepts and asked to sort them into categories. Each participant then creates a label for each category. In closed card sorts, participants are similarly given a set of key concepts, but participants are given pre-defined categories that each concept must be sorted into. Within team environments, card sorting can be used to examine the degree to which team members are thinking about key concepts in a similar manner (e.g., team mental models) by comparing the categories and sorted content across members. Each participant will complete the card-sorting task immediately following completion of the intervention and will assess CFT team mental models by examining perceptions of member roles, responsibilities, and goals across CFT team members. In doing so, the concepts contained in the card sort will be representative of specific CFT roles, task responsibilities, and goals.

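### The stated detectable effect of f² = 0.10 does not follow from 36 effective observations, and it does not hold for service linkage, which is recorded per child

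*Protocol article*

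**What the plan says.** The Power analysis section sets its own scope: "Power for the primary CFT services intervention outcomes, and team processes/emergent states outcomes, was estimated using a multi-step approach". No outcome is excepted. It counts "With 8 team members from 8 child-family teams (4 per region) participating in data collection following each of 5 child-family team meetings", for 320 observations. It then deflates for nesting: "Using conservative nesting effects for CFT members within CFT meetings, *ρ* = 0.20". The result is 36 effective observations, from which it reports that f² = 0.10 is detectable at power 0.80 and α = 0.05 on the CFT clinical intervention outcomes.

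Table 1 lists linkage under that label: "CFT Clinical Intervention Outcome Behavioral Health Service Linkage". The Participants section says linkage will be extracted from County Behavioral Health administrative data for children aged 6–17 with an identified need.

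The sampling is described in two ways. Specific aim 3 states: "This results in 8 caseworkers leading 5 CFTs each for a total of 40 unique CFTs". The Fig. 2 note states: "8 team members from 8 child-family teams (4 per region) will participate in data collection following each of 5 CFT meetings", and the Power analysis uses that second description. On caseworkers, Specific aim 3 has four in each of two regions, eight in all, while the abstract says "we will utilize blocked randomization of four CWS caseworkers from two CWS system regions".

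**The concern.** One detectable effect is offered for outcomes with different units of observation. The survey scales have about eight raters per meeting. Linkage has one administrative result per child, so neither the 320 ratings nor a correlation among members of a meeting describes the information available on it. Improving linkage is the project's stated purpose, and no other power or precision figure is given for it.

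The two sampling descriptions both multiply to 320, which hides the conflict between them. They imply about 40 or about 8 children, and either distinct teams or repeated measures on the same teams. A reader who accepts the stated sensitivity could take a null linkage result as evidence against the AAR when the trial had little chance of detecting a moderate effect.

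**Working it through.** **Inputs.** From the Power analysis: n = 320, ρ = 0.20 for members within meetings, n_eff = 36, power 0.80, α = 0.05 (sidedness not stated), claimed f² = 0.10. From Specific aim 3: 8 caseworkers, 4 per arm, 5 CFTs each. Assumed, because the article gives no values: caseworker ICC for linkage of 0.05 to 0.20, control linkage of 20% to 60%, and one index child per CFT.

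**Step 1: the plan's effective sample size.** n_eff = n/[1 + (n_clus − 1)ρ].
- n_clus = 40 (5 meetings × 8 members per caseworker): 320/(1 + 39 × 0.20) = 320/8.8 = 36.4. The stated 36 is reproduced.
- n_clus = 8 (members in one meeting, the level at which ρ is defined): 320/(1 + 7 × 0.20) = 320/2.4 = 133.

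So 36 comes from a caseworker-sized cluster combined with a meeting-level ρ.

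**Step 2: from n_eff to f².** Single-level F test with one predictor, 1 and N − 2 degrees of freedom, noncentrality f² × N.
- N = 36: noncentrality 0.10 × 36 = 3.6; power 45% (59% one-sided). Detectable f² at 80% power is 0.23 (0.18 one-sided).
- f² = 0.10 at 80% power needs N = 81 (64 one-sided).
- N = 133: power 95%; detectable f² is 0.06.

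The stated 0.10 follows from neither 36 nor 133, one-sided or two-sided.

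**Step 3: linkage on the same scale, two-sided.** With clustering, n_eff = 40/[1 + (5 − 1) × ICC].

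| Linkage values | Effective n | Detectable f² | Power for f² = 0.10 |
|---|---|---|---|
| 40 children, independent | 40 | 0.21 | 50% |
| 40, ICC 0.05 | 40/1.2 = 33.3 | 0.25 | 42% |
| 40, ICC 0.10 | 40/1.4 = 28.6 | 0.30 | 37% |
| 40, ICC 0.20 | 40/1.8 = 22.2 | 0.39 | 30% |
| 8 children | 8 | about 1.4 | 12% |

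**Step 4: linkage as linked or not linked.** Treating linkage as binary is an inference, but f² from a linear model is a poor scale if it is. With 20 vs 20 children, no clustering, and the pooled two-proportion formula, the detectable difference at 80% power is:

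| Assumed control rate | Detectable difference (percentage points) |
|---|---|
| 20% | 42 |
| 30% | 43 |
| 40% | 42 |
| 50% | 40 |
| 60% | 36 |

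Power for a 20-point difference is 24% to 28%. These figures are optimistic: by Fisher's exact test, power at the differences listed is about 68% to 75%.

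With 4 vs 4 children a normal approximation is unsuitable. By Fisher's exact test only 4/4 vs 0/4 reaches p < 0.05 (p = 0.029); 4/4 vs 1/4 gives p = 0.14.

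**The case against.** The strongest reply is that the plan does not power on 320. It carries 36 into the calculation, and 40 children is slightly more than 36. This stands. A reader might infer that the linkage claim fails because 320 shrinks to 40, but before clustering linkage is no worse off than the n the plan used (0.21 against 0.23). The main fault is the step from 36 to 0.10, which affects every outcome. What is specific to linkage is caseworker clustering, whose size is assumed, and the unresolved count of 40 or 8.

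It can also be said that no single primary outcome is named, that CSACD satisfaction, a member-rated scale, carries the same Table 1 label, and that Specific aim 3 is called a pilot test. All true, but the power statement covers the whole class without exception.

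Two stronger readings are tempting and not supported. One is that each child's linkage result will be copied about eight times into the member-level model. The Analytic plan does put child/family outcomes in a model with member as the within-meeting factor, but it does not say how linkage enters, and that may be settled in a fuller document. The other is that the card sort yields one score per team. The article describes assessing similarity "by comparing the categories and sorted content across members" but fixes no scoring rule. Both remain inferences.

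The abstract's caseworker count may mean four per region. It is ambiguous rather than clearly contradictory.

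**Conclusion.** The concern holds in this form. The claim of 80% power for f² = 0.10 is not supported at the plan's own 36 effective observations, at 40 children with or without caseworker clustering, or at 8 children. The shortfall is roughly twofold in f² at 36 or 40, up to about fourfold at an assumed ICC of 0.20, and about fourteenfold at 8. The conflict between 40 unique CFTs and 8 teams seen at 5 meetings is in the text itself and does not depend on any assumption.

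The step from 36 to 0.10 fails using only the article's figures. The linkage figures assume one index child per CFT. Siblings could raise 40 somewhat, but as correlated values. Control rates and the caseworker ICC are assumptions shown as ranges.

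**What to change.** 1. Use one sampling statement in the abstract, Specific aim 3, the Fig. 2 note and the Power analysis: either 40 unique CFTs or 8 teams over 5 meetings, with the total number of caseworkers given.
2. Limit the statement based on 320 and 36 to the member-rated scales, and correct its detectable effect to what 36 gives (f² about 0.23, two-sided). Alternatively, restate n_eff with a cluster size that matches the level of the stated ρ. Restricting the scope without correcting 0.10 would leave a wrong figure in place.
3. For linkage, state the number of children, analyse one record per child with caseworker as the cluster, and report an estimate with a confidence interval. Give its own detectable difference (about 36 to 43 percentage points at 20 vs 20 before clustering, for control rates assumed between 20% and 60%), or label the outcome exploratory.

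The cost is a change of wording and a less favourable stated sensitivity. No added enrolment or data collection is needed.

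### The detectable effect of f² = 0.10 at 80% power does not follow from the stated 36 effective observations, and the level named for ρ = 0.20 does not match the cluster size behind that 36

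*Protocol article*

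**What the plan says.** The Power analysis section of the protocol article sets out a chain of three steps.

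1. It counts observations with nesting ignored: "With 8 team members from 8 child-family teams (4 per region) participating in data collection following each of 5 child-family team meetings", so that "there is a total of 320 observation results". The section on Specific aim 3 gives the same total by another route: "Each of the 40 CFTs has ~8 participants, for a minimum total of 320 data points".
2. It penalises the total for nesting: "This was accomplished using a reorganization of the design effect formula", namely n_eff = n/[1 + (n_clus − 1)ρ]. The value of n_clus is not given. The level of ρ is: "Using conservative nesting effects for CFT members within CFT meetings", with ρ = 0.20. The result is that "the 320 observations provide statistical power equivalent to 36 independent observations".
3. It runs a conventional single-level power analysis in GPower on that effective sample size, with power 0.80 and α = 0.05. It concludes that a small-to-medium main effect of f² = 0.10 "for condition on CFT clinical intervention outcomes may be detected".

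The same 36 is then used for a separate, cautious statement on mediation. Specific aim 3 states that caseworkers are the randomised unit, 4 per condition, each followed over 5 meetings.

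**The concern.** Step 3 contains everything needed to check it: sample size, α, power, effect and method. An f² of 0.10 looks too small for 36 independent observations. Step 2 also looks inconsistent, because clusters of about 8 members per meeting would not shrink 320 to 36 at ρ = 0.20.

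The section says the calculation was done to show what effect the fixed sample can detect, so for the condition effect this f² is its main output. If 36 is right, the article claims sensitivity to an effect less than half the size of the one its own figures support. A reader could then take a null result as evidence against a small-to-medium effect when it is not.

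**Working it through.** **Inputs (Power analysis, Specific aim 3).** n = 320; about 8 members per meeting; 5 meetings per caseworker; 40 meetings; 8 caseworkers, 4 per condition; ρ = 0.20; α = 0.05; power 0.80; f² = 0.10. Sidedness is not stated, so both cases were tried. Clusters are taken as exactly 8 members and 5 meetings.

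**Step A: effective sample size**, n_eff = n/[1 + (n_clus − 1)ρ].

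- n_clus = 40 (8 members × 5 meetings per caseworker): 320/(1 + 39 × 0.20) = 320/8.8 = 36.4. This reproduces the stated 36.
- n_clus = 8 (members within a meeting, the level named for ρ): 320/(1 + 7 × 0.20) = 320/2.4 = 133.3.
- Reaching 36 with clusters of 8 would need ρ = (320/36 − 1)/7 = 1.13, which is impossible.

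So 36 follows from the stated formula, but at the caseworker level and not at the meeting level named for ρ.

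**Step B: detectable effect.** One tested predictor, noncentral F with 1 and n − 2 degrees of freedom and noncentrality λ = f²·n. For two equal arms, d = 2√f², so f² = 0.10 is d = 0.632.

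| n_eff | λ at f² = 0.10 | Power at f² = 0.10, two-sided (one-sided) | f² at 80% power, two-sided (one-sided) |
|---|---|---|---|
| 36 | 3.6 | 45% (58%) | 0.231 (0.179) |
| 133 | 13.3 | 95% (98%) | 0.060 (0.047) |

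The n needed for f² = 0.10 at 80% power is 81 two-sided, or 64 one-sided. At n = 36 the two-sided detectable effect is d = 2√0.231 = 0.96.

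**Step C: other readings of 36.** Taken as 36 per arm (n = 72), power at f² = 0.10 is 75% two-sided or 84% one-sided, and the detectable f² is 0.112 or 0.088. This does not give 0.10 either, and the text presents 36 as the equivalent of all 320 observations.

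**Step D: sensitivity to the number of caseworkers.** Suppose ρ = 0.20 applies at caseworker level and the test uses the 8 − 2 = 6 degrees of freedom between caseworkers. Then λ = 0.10 × 36.36 = 3.64 and power is about 36%. The detectable f² is about 0.312, or d = 2√0.312 = 1.12.

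**The case against.** The strongest reply is that 36 is defensible. Forty observations per caseworker is a structure the Power analysis section itself describes, and the caseworker is the randomised unit, so 40 is a reasonable cluster size for a test of condition. This stands. A reader might infer that 36 is an error, or that the count of 40 meetings was entered by mistake as a cluster size. The article does not support that, because n_clus is not stated and 36 follows from its own formula. What is shown is a mismatch between the level named for ρ and the cluster size used.

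A second reply is that the two discrepancies pull in opposite directions. If the description of ρ is right, n_eff is 133 and f² = 0.10 is conservative. This also stands, so over-optimism cannot be asserted without the condition that 36 holds.

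Third, some calculations do land near 0.10. An omnibus test of 5 predictors at n = 133 detects 0.101. A repeated-measures between-factor calculation on 36 with 5 measures detects 0.083 at correlation 0.2 and 0.139 at 0.5. None of these matches the text. The first is not a main effect of condition and does not use 36. The second counts the repeated observations a second time, after the design effect has already been applied.

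Finally, Aim 3 is described as a pilot test, the sample was fixed before the calculation, and no decision rule depends on f² = 0.10. That limits the consequence but does not make the figure correct.

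**Conclusion.** The stated detectable effect is wrong on its own inputs. With the article's 36 effective observations, power at f² = 0.10 is about 45%, not 80%. The 80%-power effect is f² = 0.23, more than twice the stated value and medium-to-large rather than small-to-medium. A one-sided test does not close the gap (58% and 0.18). Separately, the level given for ρ implies 133, for which the figures are f² = 0.06 and 95% power. No reading of the described method gives 0.10. The direction of the error depends on which effective sample size the authors intended, although the article itself relies on 36 twice.

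A reader might go further and infer that every power statement in the section is wrong. That is not supported. The mediation statement is hedged and agrees with 36: it cites required sample sizes of 35 to 74 and calls 36 potentially sufficient only if both paths have large effects. Nor does the error show that the sample must change, because the calculation did not set it.

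The results assume equal clusters, equal arms and a single tested predictor. The 6-degree-of-freedom figures further assume that ρ = 0.20 holds at caseworker level, which the article does not say.

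**What to change.** In the Power analysis section, state the value of n_clus and the level to which ρ = 0.20 applies, and recompute the detectable effect from the resulting n_eff.

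- If 36 stands: describe ρ as nesting within caseworker, and replace the small-to-medium main effect of f² = 0.10 by a medium-to-large main effect of f² = 0.23 (d about 0.96).
- If nesting within meetings is meant: replace 36 by 133 and give f² = 0.06. The mediation sentence, which uses 36, then has to be revised as well.
- Optionally, add that if ρ = 0.20 is assumed at caseworker level, a test on 8 caseworkers with 6 degrees of freedom has about 36% power at f² = 0.10 and detects d of about 1.12.

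The cost is a change of text. Sample and design stay as they are. If 36 stands, the stated sensitivity becomes less favourable.
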